## Abstract

**Background:**

Different physical activities are widely recommended as non-pharmacological therapies to reduce blood pressure. However, the effectiveness of exercise programs is associated with its continuity and regularity, and the long-term adherence to traditional exercise interventions is often low. Recreational sports emerge as an alternative, being more captivating and able to retain individuals for longer periods. Besides, sport interventions have demonstrated improvements in physical fitness components that are associated with a lower incidence of hypertension. However, no studies have investigated the effects of recreational sports on 24 h ambulatory blood pressure. The aim of the present study is to evaluate the effect of beach tennis training on ambulatory blood pressure and physical fitness in individuals with hypertension.

**Methods:**

This study will be a randomized, single-blinded, two-arm, parallel, and superiority trial. Forty-two participants aged 35–65 years with previous diagnosis of hypertension will be randomized to 12 weeks of beach tennis training group (two sessions per week lasting 45–60 min) or a non-exercising control group. Ambulatory (primary outcome) and office blood pressures, cardiorespiratory fitness, muscle strength/power and quality of life will be assessed at baseline and after the intervention period.

**Discussion:**

Our conceptual hypothesis is that beach tennis training will reduce ambulatory blood pressure and improve fitness parameters in middle-aged individuals with hypertension. The results of this trial are expected to provide evidences of efficacy of recreational beach tennis practice on blood pressure management and to support sport recommendations for clinical scenario in higher risk populations.

**Trial registration:**

ClinicalTrials.gov, NCT03909321. Registered on April 10, 2019.

## Background

Hypertension is considered the most important modifiable risk factor for cardiovascular disease [1, 2] affecting nearly one-third of adults in Brazil [3] and worldwide [4] with increased prevalence throughout lifespan [5]. Although the usual treatment of hypertension is based on blood pressure lowering drugs, changes in lifestyle through physical exercise has emerged as an effective strategy for prevention and treatment of this condition [6]. A number of studies have shown that aerobic, resistance and combined training can reduce 24 h ambulatory blood pressure in hypertensive participants [7, 8].

The effectiveness of physical exercise programs seems to be directly associated with its continuity and regularity, and the long-term adherence to traditional exercise interventions (i.e., resistance and aerobic training) is often low [9]. One of the problems raised by individuals who do not adhere to exercise is the monotony and smaller motivation that those activities provide to their practitioners [10]. In this regard, recreational sports emerge as an alternative, being more captivating and able to retain individuals for longer periods and to sustain prolonged benefits to its practitioners [11, 12]. Promising results have been described with the use of recreational team sports on cardiovascular parameters [10, 13], including reduced BP in the office among participants with hypertension [14]. Although office blood pressure can be used to assess and diagnose hypertension, data assessing blood pressure through ambulatory blood pressure monitoring can provide additional information related to the benefits of recreational sports on blood pressure management, and future studies should investigate the effects of recreational sports on 24 h blood pressure.

The age-related decline in physical fitness components (i.e., cardiorespiratory fitness, muscular strength and power, balance, among others) [15] and physical activity levels [16] are also associated with increased prevalence of cardiovascular diseases. Different recreational sports, especially soccer [17] and other contact team sports [18, 19], have been studied over the last 10 years, suggesting that different sports could be effective for improving physical fitness and could be important for reducing risk of hypertension [20, 21]. In this regard, other sports modalities that can be practiced by middle-aged and older adults should be investigated to provide more information on this topic.

Although participation in recreational sports can be enjoyable, it may also face some difficulties to obtain high adherence, particularly due to musculoskeletal injuries [22]. Invasion sports, which usually demands a higher number of participants during the game, are prone to promote injuries [23]. Alternatively, sports with no physical contact and performed with few participants can be advantageous to improve participation [24]. In particular, beach tennis emerges as an interesting option based on easy accessibility, necessity of few participants to play, and lower risk of injury compared to traditional invasion sports [25]. Beach tennis is a racket sport played on a smaller sand court instead of the traditional tennis court, usually on the beach. It can be performed by different age groups and levels of conditioning/skills with only 2 to 4 participants per game. Nowadays, it is estimated that more than a million people practice the sport worldwide [25], and around sixty thousand practitioners in Brazil, a growth that represents an increase in the number of practitioners from 150 to 200% in the last year [26]. Recently, our research group evaluated the acute effects of a single session of beach tennis on different cardiovascular parameters in hypertensive individuals. During 45 min of beach tennis practice, the participants presented an average reserve heart rate (HR_reserve_) of 59–68% and there were no reported adverse events, confirming the potential of this sport to improve the cardiovascular profile in individuals with hypertension (Unpublished data; Trial registration: ClinicalTrial.gov n° NCT03909308).

To the best of our knowledge, no studies have investigated the chronic effects of team sports on 24 h ambulatory blood pressure and have assessed the effects of a beach tennis intervention in cardiovascular profile and physical fitness. Based on that, we designed this parallel randomized controlled trial to evaluate the effect of beach tennis training on 24 h ambulatory blood pressure and different physical fitness parameters in individuals with hypertension. The difference between the intervention arms in mean change from baseline in 24 h, daytime and nighttime systolic and diastolic ambulatory blood pressure at 12-weeks is the primary outcome; secondary outcomes are the difference between mean change in office blood pressure as well as cardiorespiratory fitness, muscular strength and power. We anticipate that 12 weeks of beach tennis training will reduce blood pressure when compared to a non-exercising control group. Additionally, our recreational beach tennis intervention will improve all physical fitness components in comparison to the baseline values.

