#### Secondary outcomes

Secondary outcomes include the average change in office systolic and diastolic blood pressure as well as cardiorespiratory fitness, muscular strength and power and quality of life evaluated at baseline and after 12-week intervention in both arms. Additional measures of office blood pressure and enjoyment level during beach tennis sessions will be assessed at weeks 1, 4, 5, 8, 9 and 12.

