**Fig. 1 Fig1:**
[figure not shown]
Recruitment and randomized allocation group from the CONSORT 2010 flow diagram

Those who signed the consent will undergo a clinical screening, resting electrocardiogram, anamnesis with sociodemographic, anthropometric and clinic data assessment, and questionnaire to evaluate quality of life. After that, the participants will perform a familiarization with strength and power muscle tests and with the mask that will be used in the cardiopulmonary test. In the second visit, participants will place the equipment of ambulatory blood pressure monitoring. On the day after, each participant will return at the laboratory to remove the equipment and perform evaluations of the cardiorespiratory fitness, muscular strength and power. All variables are assessed at baseline and at study completion. Participants will be asked to maintain their habitual activity and dietary habits at the time of recruitment.

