### Statistical analysis

The endpoints will be analyzed using a full analysis set including all randomized participants, therefore allowing intention-to-treat analyses. A second set of per-protocol analysis will be performed including participants that completed the trial with adherence to at least 80% of the beach tennis intervention sessions (≥ 19 sessions for participants allocated in the BTT program).

Data distribution will be analyzed using Shapiro-wilk test with analysis of histogram and Q-Q plots in combination. Data will be expressed as means and standard error for variables with normal distribution or medians and interquartile range for non-normal distributions and 95% confidence intervals (95%CI). Ambulatory blood pressure will be analyzed as daytime, nighttime and 24 h systolic and diastolic blood pressure. Primary and secondary outcomes will be analyzed using generalized estimating equation model (GEE) for correlated measures. Adjustment for multiple comparisons will be accomplished using Sequential Bonferroni test. All analysis will be conducted using SPSS Statistics for Windows, version 18.0 (IBM corp., Armonk, NY, USA).

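### The fitness hypothesis is worded against the trained arm's own baseline, which contradicts the protocol's definition of the fitness outcomes as a between-arm difference in change

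*Protocol article*

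**What the plan says.** Three consecutive sentences at the end of the Background section matter here.

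- The outcome definition opens with the difference between the intervention arms in mean change from baseline for ambulatory blood pressure, and continues: "secondary outcomes are the difference between mean change in office blood pressure as well as cardiorespiratory fitness, muscular strength and power". Read as one sentence, this makes fitness a between-arm difference in change.
- The blood pressure hypothesis names the control arm as comparator: "12 weeks of beach tennis training will reduce blood pressure when compared to a non-exercising control group".
- The fitness hypothesis names baseline as comparator: "our recreational beach tennis intervention will improve all physical fitness components in comparison to the baseline values".

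Elsewhere, the abstract describes the design: "This study will be a randomized, single-blinded, two-arm, parallel, and superiority trial". The Secondary outcomes section refers to average change, with the measures "evaluated at baseline and after 12-week intervention in both arms". The Statistical analysis section says "Primary and secondary outcomes will be analyzed using generalized estimating equation model (GEE) for correlated measures", on a full analysis set of all randomised participants, and adds "Adjustment for multiple comparisons will be accomplished using Sequential Bonferroni test". The text under Participant timeline and data collection says that, before baseline testing, "the participants will perform a familiarization with strength and power muscle tests and with the mask that will be used in the cardiopulmonary test".

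**The concern.** The same paragraph gives two success criteria for the fitness outcomes. Under the outcome definition, beach tennis succeeds if fitness improves more than in controls. Under the hypothesis, it succeeds if fitness in the trained arm is better at 12 weeks than at baseline. Because the preceding sentence takes care to name the control group, the second criterion is hard to read as shorthand for the first.

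The two criteria can give different answers. Jump, throw, chair-stand, handgrip and treadmill performance depend on effort and on practice with the test. A change from baseline mixes the training effect with retest gain, motivation and the passage of time. The control arm has the same tests at the same times so that these can be subtracted. A trial in which both arms improved equally would meet the hypothesis as written, yet would show no effect of beach tennis.

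**Working it through.** **1. The comparators side by side**

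| Statement in Background | Comparator |
|---|---|
| Definition of primary and secondary outcomes | Other arm (difference in mean change) |
| Blood pressure hypothesis | Control group |
| Fitness hypothesis | Own baseline |

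Only the third departs from the between-arm comparison.

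**2. What a shared gain does to each criterion**

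The article gives no power or sample size for any fitness measure, so there is no stated figure to reproduce. Inputs:

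- Arm sizes of 28 and 14, from Sample size and power calculation.
- Dropout of 10% from the same section: 28 × 0.9 = 25.2, taken as 25.
- Two-sided 5% test, assumed for illustration (the article gives a 5% type I error rate without saying how many sides).
- Shared retest or time gain *g*, in SDs of the change score. The article gives none, so *g* is assumed over the range 0 to 0.5.
- True training effect set to zero.

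Within-arm test: one-sample *t* on post minus baseline. The chance of a significant improvement is P(T > t₀.₉₇₅,ₙ₋₁), where T is noncentral *t* with n − 1 degrees of freedom and noncentrality g√n. For n = 28 and g = 0.3, the noncentrality is 0.3 × √28 = 1.587, the critical value is 2.052, and the probability is 0.334.

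| Assumed *g* (SD of change) | n = 28 | n = 25 |
|---|---|---|
| 0 | 2.5% | 2.5% |
| 0.1 | 7.4% | 6.9% |
| 0.2 | 17.4% | 15.9% |
| 0.3 | 33.4% | 30.2% |
| 0.4 | 53.2% | 48.4% |
| 0.5 | 72.3% | 67.0% |

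Between-arm test: the expected difference in change is g − g = 0 whatever *g* is, so the error rate stays nominal. Simulation of a two-sample *t* test on change scores (28 versus 14, 50,000 runs each at g = 0, 0.2, 0.3 and 0.5) gave a false improvement in 2.4% to 2.5% of runs, and significance in either direction in 4.8% to 5.1%.

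**3. Effect of the planned multiplicity adjustment**

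The table is unadjusted, and the article does not state the family for the Sequential Bonferroni procedure. As an assumption, take the six pairwise comparisons of a two-arm, two-time layout. The strictest step is then 0.05/6 = 0.0083. At that level the within-arm probabilities with n = 28 are about 5%, 12%, 26% and 44% for g = 0.2, 0.3, 0.4 and 0.5. Later steps are less strict, so for that family these are lower bounds and the unadjusted figures are upper bounds. Adjustment lowers the rates. It does not remove the bias, because the within-arm change still estimates training effect plus *g*.

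**The case against.** The strongest reply is that the quoted sentence is an expectation in the Background section, not an analysis rule, and that everything operational keeps the control. The outcome is defined between arms, both arms are tested, and the GEE covers all randomised participants. This stands. A reader might infer that the trial discards its randomised control for fitness; the article does not support that, and the fault is confined to the hypothesis sentence and its conflict with the outcome definition.

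A reader might also count it as an error that the Statistical analysis section does not name the model term to be tested. A condensed article commonly leaves that to the full protocol or analysis plan, so it is no finding here. Nor does the article say that within-arm tests will support efficacy claims.

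The familiarisation session is a further fair point. It is aimed at practice effects in the strength and power tests, so the five tests are not equally exposed. It reduces retest gain there but may not remove it, and for the treadmill test it covers only the mask.

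Finally, one could argue that unequal arm sizes would make a gain significant in the 28 and not in the 14, and so invite a false claim of difference. That requires comparing significance between arms, which the article nowhere proposes, so the point does not rest on it.

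What survives these replies is the contradiction itself. It is a matter of what is stated, not of missing detail, and an analysis plan that named the right contrast would still leave the published hypothesis at odds with it.

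**Conclusion.** The point holds as an internal contradiction: a within-arm hypothesis set against a between-arm outcome definition for the same fitness measures. A gain shared by both arms would satisfy the hypothesis as worded.

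With no training effect, the chance of a false improvement for one fitness measure ranges from 7% at a shared gain of 0.1 SD to 72% at 0.5 SD (n = 28, unadjusted), against about 2.5% for the between-arm contrast. These figures rest on assumed gains and on normally distributed change scores. They show how far the two criteria can diverge; they do not predict what this trial will find. If familiarisation removes most of the retest gain, the low end of the range applies to the strength and power tests.

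Severity is minor to moderate: only secondary outcomes are affected, and the article already contains the correct definition.

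**What to change.** Restate the fitness hypothesis so that it matches the outcome definition: beach tennis training will improve each fitness measure more than control over 12 weeks. Base fitness efficacy conclusions on the arm-by-time contrast from the planned GEE, or on the baseline-adjusted difference between arms, and report within-arm changes as descriptive only.

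The cost is one sentence in the Background section and, if wanted, one in the Statistical analysis section. No new data, participants or change of model are needed.

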## Methods/design

### Study design

This is a single-center, two-arms, parallel randomized controlled trial with concealed allocation, blinded measurers, with 12 weeks of follow-up analyzed using an intention-to-treat approach. The recruitment will take place between December 2020 and December 2021 through social media and banners. The protocol followed the recommendations for interventional trials (SPIRIT) 2013 guidelines [27].

### Study setting

The primary site of this study is the Center of Clinical Research at Hospital de Clínicas de Porto Alegre (Porto Alegre, RS, Brazil). The intervention center takes place at indoor and outdoor beach tennis courts (Porto Alegre, RS, Brazil), located outside to the hospital.

Inclusion criteria:
Men and women (aged 35–65 years) with previous diagnosis of hypertension and using up to 3 of any class or type of anti-hypertensive drugsNot engaged in structured exercise programs in the 3 months prior to the start of the studyAble to be enrolled, based on resting electrocardiogram (do not present arrhythmias, conduction disorders, coronary ischemic conditions or pathophysiological and structural abnormalities of the heart) and questionnaire about the participant’s clinical and osteoarticular symptomsSigned a written consent form for participation in the study

Exclusion criteria:
Cardiovascular disease detected by acute myocardial infarction, angina, stroke or heart failure diagnosed in the last 24 months, as well as other chronic diseases (cancer, chronic heart failure with NYHA classes III or IV, kidney disease requiring dialysis, multiple sclerosis, Parkinson’s disease, among others)Current smokers or non-smokers for less than 6 monthsBody mass index over than 39.9 kg/m^2^Diabetic proliferative retinopathy

### Interventions

Participants will be randomly allocated to the beach tennis training intervention (BTT) or to the control group (Con), which will not be submitted to intervention and will be instructed not to engage in any kind of structured physical exercise training and to keep the life activities identified at baseline. The International Physical Activity Questionnaire (IPAQ) will be applied before and after the intervention in order to assess the level of physical activity.

#### Beach tennis training

In BTT, supervised beach tennis sessions will be performed two times per week. Each session will be composed of an initial period of 10 min of warm up and technical exercises (i.e., serve, volley, forehand and backhand). After that, 3 games of 10–15 min each (weeks 1–4: 3 × 10 min; weeks 5–8: 3 × 12 min; and weeks 9–12: 3 × 15 min) with an interval of 2 min between each game will be played in pairs (i.e., 2 versus 2). In case of less than 4 participants are able to play at the same time, the games can also be played individually (i.e., 1 *versus*1). As an objective measure of exercise intensity, heart rate (HR) will be continuously recorded with a Polar HR monitor (Polar FT7, Finland) during the beach tennis sessions, and data related to the average HR_reserve_ and maximal HR will be used to characterize the intensity throughout the sessions. We previously tested the physiological demand of beach tennis practice using the same methods and found an average HR of 59–68% HR_reserve_ during the beach tennis session lasting 45 min in participants with hypertension (Unpublished data; Trial registration: clinicaltrials.gov n° NCT03909308).

During the first week of beach tennis training, the participants will perform one or two familiarization sessions on the sand court in order to introduce basic beach tennis rules and game techniques. If necessary, one extra familiarization session will be allowed to those who need more practice to be able to play the game. Based on these familiarization sessions, two research team members with previous experience in beach tennis will classify each participant into three categories: beginner (poorly coordinated racket movements and little movement on the court), intermediate (more agile and coordinated movements), or advanced (broad dominance in all aspects of the game), in order to organize the schedule of beach tennis sessions by matching players of the same performance level. We believe that ensuring high motivation and adequate intensity during any sport practice is important and to organize the games using participants at a similar performance level will help to get it. *Control group -* In Con, participants will be advised to not change their daily usual activities and to not participate in any structured physical exercise program during this period. At the end of the study period after completing pre and post intervention assessments, we will offer 4 weeks of beach tennis practice to the participants of the control group.

### Outcome measurements

Outcomes will be assessed for all randomized participants before and after the intervention sessions, irrespective of attendance or completion status. For participants who drop-out of the study at any time after the randomization, researchers will use contact information to invite such participants to undergo the end-study outcome assessments (12 weeks after the beginning of intervention).

#### Primary outcome

The primary outcome is the change from baseline in 24 h, daytime and nighttime systolic and diastolic blood pressure measured by ambulatory blood pressure monitoring at 12 weeks.

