### Sample size and power calculation

Sample size for the primary outcome was calculated using estimates of effect sizes from randomized clinical trial with similar design [14]. This estimation was set a priori based on a behavioral intervention for middle-aged patients with hypertension and analyzed in an intention-to-treat approach. A sample size of 42 individuals with hypertension on 2:1 ratio (BTT, *n*= 28) and (Con, *n*=14) allowing a dropout rate of 10%, will be able to detect a difference of 4 ± 6 mmHg in systolic 24 h blood pressure between groups. Statistical power was set at 90% including a type I error rate of 5%. WinPepi software calculator was used to estimate the sample size [35].

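### Six ambulatory pressures share primary status, but the sample size covers only 24 h systolic; no reading of the multiplicity sentence keeps both the 5% error rate and the 90% power

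*Protocol article*

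**What the plan says.** The Primary outcome section reads: "The primary outcome is the change from baseline in 24 h, daytime and nighttime systolic and diastolic blood pressure", assessed at 12 weeks. The Background repeats the same set as a between-arm difference in mean change: "24 h, daytime and nighttime systolic and diastolic ambulatory blood pressure at 12-weeks is the primary outcome". Three periods and two pressures make six measures.

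The section Sample size and power calculation says that it serves the primary outcome, but it uses one of the six. The planned 28 and 14 participants, with 10% dropout allowed, "will be able to detect a difference of 4 ± 6 mmHg in systolic 24 h blood pressure between groups". Power is set at 90% and the type I error rate at 5%; no allowance for several primary measures is mentioned.

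The Statistical analysis section lists all six pressures again, without ranking them. It then states: "Primary and secondary outcomes will be analyzed using generalized estimating equation model (GEE) for correlated measures". The next sentence is: "Adjustment for multiple comparisons will be accomplished using Sequential Bonferroni test". It does not say which comparisons form the family.

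**The concern.** The outcome declared primary is not the outcome for which the trial was sized. The sample size section presents 5% and 90% as properties of the trial's primary test. They can hold together only if 24 h systolic is tested alone, or first in a fixed order. The article states neither.

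What counts as a successful trial is therefore open. A difference confined to, say, nighttime diastolic pressure might or might not count as a positive primary result, depending on how a one-line adjustment sentence is read. Under one reading the trial-level false-positive rate exceeds 5%. Under the other, the measure on which the trial was sized is tested more strictly than planned.

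**Working it through.** **Inputs.** From the article: six primary measures; allocation 28 and 14; two-sided 5% (the article does not state sidedness, so two-sided is assumed); 90% power; daytime from 7 AM and nighttime from 11 PM, with readings every 15 and 20 minutes (Measurement of primary outcome). Assumed, because the article gives no correlations: day-night correlation 0.3 to 0.8 and systolic-diastolic correlation 0.5 to 0.8.

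**1. The plan's own figure.** Read "will be able to detect a difference of 4 ± 6 mmHg in systolic 24 h blood pressure between groups" as a difference of 4 mmHg with SD 6 mmHg.
- Control-group size at 2:1: (1 + 1/2) × 6² × (1.960 + 1.282)² / 4² = 35.5, rounded up to 36. The total is 36 + 72 = 108 evaluable, and 108 / 0.9 = 120 with dropout. The article states 42.
- For 28 and 14, the noncentrality is 4 / (6 × √(1/28 + 1/14)) = 2.04, which gives 51% power by the noncentral t.
- For 25 and 13 after dropout, the noncentrality is 1.95, which gives 48%.

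The stated 90% does not reproduce, and this has nothing to do with multiplicity. To isolate the multiplicity effect, the steps below take the 90% at face value.

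**2. Reading A: the adjustment applies to comparisons within each model, so the six measures are each tested at 5%.** Planned readings are 16 h × 4 = 64 by day and 8 h × 3 = 24 by night. The 24 h mean is therefore (64 × day + 24 × night) / 88, separately for systolic and diastolic. Six two-sample t-tests were simulated under no effect with 28 and 14 participants. The chance of at least one p < 0.05 was:

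| Day-night correlation | Systolic-diastolic 0.5 | Systolic-diastolic 0.8 |
|---|---|---|
| 0.3 | 18% | 16% |
| 0.5 | 17% | 14% |
| 0.8 | 15% | 12% |

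The range is about 12-18%, against a stated 5%.

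**3. Reading B: the adjustment spans the six.** The family-wise error is at most 5%. The first step uses 0.05 / 6 = 0.0083, with critical value 2.638.
- A test with 90% power at 5% has an expected z of 1.960 + 1.282 = 3.242. At the first step its power is Φ(3.242 − 2.638) = Φ(0.603) = 73%.
- Sequential Bonferroni relaxes the threshold after each rejection. If all six pressures share the same standardised effect, simulated power for 24 h systolic is about 80-85% over equal correlations from 0.9 down to 0. This is still short of 90%.
- Keeping 90% at the first step multiplies the sample by ((2.638 + 1.282) / 3.242)² = 1.46, which is about 62 instead of 42.

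**4. Reading C: all six must be significant at 5%.** Error is controlled, but power to win on all six is 78% at an equal correlation of 0.8 and 82% at 0.9, even if every measure has 90% power on its own.

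None of the three readings keeps both 5% and 90%.

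**The case against.** The strongest reply is that the article does prespecify an adjustment, and that a condensed article may leave the exact alpha family to an analysis plan that is not shown. The absence of that detail is not, by itself, a fault. What stands is narrower: the article itself fixes both the primary outcome (six measures) and the sample-size target (one measure), and the two do not match. A later analysis plan that picked one of the six would be changing the published primary outcome.

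Three stronger inferences are tempting, and the document does not support them.
- *Any one significant pressure of six counts as success.* The article states no such rule, and it does state an adjustment. This is one possible reading only.
- *The false-positive rate is 26%.* The figure 1 − 0.95⁶ = 26.5% needs six independent tests. The 24 h value is made from the daytime and nighttime readings, so independence is impossible.
- *Multiplicity cuts power to 22-25%.* That is the first-step power at 0.0083 on the printed 4 mmHg and SD 6 mmHg. It starts from a baseline of 48-51%, so most of the shortfall from 90% belongs to the sample-size calculation.

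It is also fair that the sample size section already singles out 24 h systolic. It does not call it the sole or leading measure, and the Primary outcome and Background sections contradict that idea.

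**Conclusion.** The mismatch is real and lies in the text as stated. Either the 5% becomes about 12-18% (no adjustment across the six), or error is controlled and the planned 90% for 24 h systolic becomes about 73% at the first step, with less loss if other pressures are rejected first. The first range rests on the assumed correlations and on weighting by the planned reading intervals. The second takes the article's 90% at face value.

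That 90% is itself not supported by the printed difference, SD and sample size. This is a separate defect, and resolving the choice of primary outcome leaves it in place.

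**What to change.** Name one primary outcome: the between-group difference in change from baseline to 12 weeks in 24 h systolic pressure, tested at two-sided 5%. It is already the sample-size variable, so the primary outcome and the sizing would then refer to the same test. Make the other five ambulatory pressures secondary, and state that Sequential Bonferroni, or a fixed order, applies across those five. Use the same wording in the Background, Primary outcome and Statistical analysis sections.

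A fixed testing order that starts with 24 h systolic would also protect both figures, if the investigators want to keep the other pressures within the primary family.

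The cost is a change of wording, dated and made before outcome data are seen by group. No participant, visit or measurement is added. The small downside is that five measures lose primary status. The registry record was not available, so whether it needs the same change cannot be judged here.

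Separately, 4 ± 6 mmHg must be reconciled with 42 participants; this change does not do that.
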